## Abstract

**Introduction:**

Tuberculosis (TB) transmission is difficult to measure, and its drivers are not well understood. The effectiveness of infection control measures at healthcare clinics and the most appropriate intervention strategies to interrupt transmission are unclear. We propose a novel approach using clinical, environmental and position-tracking data to study the risk of TB transmission at primary care clinics in TB and HIV high burden settings in sub-Saharan Africa.

**Methods and analysis:**

We describe a novel and rapid study design to assess risk factors for airborne TB transmission at primary care clinics in high-burden settings. The study protocol combines a range of different measurements. We will collect anonymous data on the number of patients, waiting times and patient movements using video sensors. Also, we will collect acoustic sound recordings to determine the frequency and intensity of coughing. Environmental data will include indoor carbon dioxide levels (CO_2_ in parts per million) and relative humidity. We will also extract routinely collected clinical data from the clinic records. The number of *Mycobacterium tuberculosis* particles in the air will be ascertained from dried filter units using highly sensitive digital droplet PCR. We will calculate rebreathed air volume based on people density and CO_2_ levels and develop a mathematical model to estimate the risk of TB transmission. The mathematical model can then be used to estimate the effect of possible interventions such as separating patient flows or improving ventilation in reducing transmission. The feasibility of our approach was recently demonstrated in a pilot study in a primary care clinic in Cape Town, South Africa.

**Ethics and dissemination:**

The study was approved by the University of Cape Town (HREC/REF no. 228/2019), the City of Cape Town (ID-8139) and the Ethics Committee of the Canton Bern (2019-02131), Switzerland. The results will be disseminated in international peer-reviewed journals.

Strengths and limitations of this studyWe describe the protocol for a prospective study design to studying tuberculosis (TB) transmission in primary care clinics in high TB/HIV-burden settings.This rapid approach will combine a wide range of different measurements, including patient waiting times and movements, acoustic recording of coughing, measurement of carbon dioxide levels as a natural tracer gas, air humidity and semiquantitative detection of *Mycobacterium tuberculosis* (Mtb) particles in the air.We will develop a mathematical model which will integrate the collected data to estimate the risk of TB transmission, identify key drivers of transmission and evaluate the impact of infection control measures such as improved ventilation or wearing masks.The main limitation of this study design is the lack of direct observation of transmission events and the reliance on the number of Mtb particles in the air as a proxy for TB transmission.Study limitations pertain to the need for stable electricity and WiFi for data collection.

## Introduction

Tuberculosis (TB), caused by the bacterium *Mycobacterium tuberculosis (*Mtb), remains a major global public health problem, particularly in the context of HIV and drug resistance. Sub-Saharan Africa is one of the most heavily burdened regions globally, although control measures have been in place since the beginning of the 20^th^ century.^1^ Over a century of investment in TB control has reduced TB mortality, but effective strategies are urgently needed to reduce TB transmission.^2^ Drivers of the TB epidemic in sub-Saharan Africa are HIV-infection and the resulting immunodeficiency (the strongest risk factor),^1^ delayed diagnosis and treatment as well as undetected and untreated cases of TB or drug-resistant TB. These factors allow patients with infectious TB to transmit Mtb to the community.^3–5^ There are still many gaps in our knowledge on TB transmission such as the factors and locations associated with the risk of transmission, the effectiveness of infection control measures at clinics in high-burden settings and the most appropriate intervention strategies to interrupt transmission.^5–7^

For TB transmission to occur, infected individuals must expel Mtb bacilli from their respiratory tract, and an uninfected individual must inhale aerosols containing live bacilli to become infected. Transmission of Mtb is difficult to measure due to the lack of an in vitro test assay. The preferred approach is to measure presumptive transmission resulting in secondary cases as determined by molecular/genomic epidemiology. TB transmission has traditionally been investigated using contact tracing, analyses of geo-temporal clustering and molecular typing.^8 9^ However, molecular methods require resource-intensive culturing of strains and measure only transmission resulting in secondary cases. Furthermore, contact tracing is difficult to implement in resource-limited settings and may not be an effective control strategy in endemic areas where casual contacts are increasingly recognised as an important contributor to transmission.^10^ New approaches are therefore urgently needed.

Mtb is carried in airborne particles (called infectious droplets), which are generated when people with TB cough, sneeze or shout.^5^ Indoor carbon dioxide (CO_2_) levels can be used to assess the amount of exhaled air in a room and the amount of rebreathed air.^11–13^ Humidity is associated with Mtb survival in the air.^14^ Viable Mtb particles have been captured from contaminated air.^11 15–17^ We describe a unique study design to assess risk factors for airborne TB transmission in primary care clinics in high TB/HIV-burden settings. The approach combines a range of relevant measurements, including data on patient and infrastructure, movements of patients through the facility, coughing, environmental indoor CO_2_ levels and concentration of Mtb particles in the air.

We hypothesise that (1) exposure to Mtb particles at the clinic can be estimated by studying the patient flow and CO_2_ levels; (2) the number of individuals present, the rebreathed fraction and the frequency of coughs influence exposure to Mtb; (3) clinics with small and crowded waiting rooms, low ventilation and suboptimal patient separation have an increased risk of TB transmission.

## Methods

### Study design

Longitudinal study with data collection at the levels of the patients, the clinic and the environment. Data collection will take place for over 4 weeks. Figure 1 shows the floor plan of an exemplary primary clinic with the planned study activities, including the recording of patient movements, coughing, CO_2_ levels and Mtb particles in the air.

**Figure 1 F1:**
[figure not shown]
Floor plan of the pilot primary care clinic in Cape town, South Africa, indicating study measurements. Mtb, *Mycobacterium tuberculosis*; TB, Tuberculosis.

### Study setting and study population

The study will take place at several antiretroviral therapy (ART) or primary care clinics in countries participating in the International Epidemiology Database to Evaluate AIDS (IeDEA) in Southern Africa collaboration with a high TB and HIV burden.^18^ These clinics are located in urban and peri-urban communities with predominantly young and black African residents. TB and HIV are both prevalent in these communities.

### Patient-level variables

#### Video sensor data

A person-tracking sensor system developed by Xovis (Zollikofen, Switzerland and Cambridge, Massachusetts, USA; see www.xovis.com) will be used to monitor the clinic attendees’ movements. The data will be used to calculate waiting times, the number of people in different locations and the average distance between people, and to identify highly frequented areas. Several sensors will be installed to cover the clinic area, calibrated and validated. Sensors with overlapping ranges will be combined for the seamless coverage of people’s movements over large areas (figure 2). The raw data consist of the person’s height, time, date and the position (x–y coordinates) for each unique individual during the duration of their stay within the clinic. The data are captured every 0.25 s. The raw data are then parsed by a python script to calculate the height, total movement and observation time at different locations, and to visualise hotspots.

**Figure 2 F2:**
[figure not shown]
Output from video sensors with moving dots showing the tracked persons. The numbers in the dots indicate the height of patients. The different sectors covered by the sensors are merged images from the pilot study.

The sensors have four levels of privacy. In our study, privacy will be set to level 2, which means that the data are a fully anonymised stream of the coordinates of moving dots. These dots will be linked probabilistically to the anonymised clinical data thus excluding any risk of re-identification. Further, the images of tracked individuals taken by the sensors will not be stored (see also the data privacy and security statement by Xovis).^19 20^

#### Patient and clinic data

We will extract clinical data from the electronic patient registry for all patients who visited the clinics during the 4 weeks of data collection. The data will include date and time of registration, age, sex, height (used for linkage with video sensor data), HIV status, presumptive TB (‘TB suspects’), mode of TB diagnosis (sputum smear microscopy, Xpert MTB/RIF, mycobacterium culture), TB diagnostic test results, date of TB treatment start and current anti-TB treatment regimen. We will not extract any personal data, such as names or social security numbers. The clinic-level data will include information such as the setting (urban or rural), level of care, the number of patients seen each year, availability of adult and paediatric care, TB control measures (natural ventilation, use of masks, separation of patients with TB or coughers) and the floor plan of the clinics. The data will be collected using the web-based REDCap Data Entry System (www.redcap.org).^21^

### Definitions

Presumptive TB refers to a patient who presents with clinical symptoms or signs suggestive of TB. A bacteriologically confirmed TB case is a person for whom a biological specimen is positive by smear, microscopy, culture or rapid diagnostic such as Xpert MTB/RIF or line probe assay.^22^

### Environmental variables

#### Co_2_, relative humidity and temperature monitoring

We will use CO_2_ monitors (Digital CO_2_ Monitor Carbon Dioxide Metre XE-2000, XEAST, Guangdong, China) which include the COZIR-A sensor for ambient CO_2_ levels of 0%–1% (Gas Sensing Solutions, Cumbernauld, Scotland). The monitors will record indoor CO_2_ concentrations (in parts per million (ppm)), temperature and relative humidity at minute intervals. Data from the five monitors are stored and exported in serial digital format.^15 16^ At each clinic we will install five monitors to cover the most visited spaces and a control area outside the clinic (figure 1). The monitors auto-calibrate over time to a standard minimum value of 400 ppm. This value is close to the average monthly outdoor carbon dioxide concentration measured at Cape Point, South Africa (405.48 ppm in December 2018).^23^ Monitors will be run for 1 week before the start of the study to allow them to calibrate and to confirm that they delivered comparable data.

#### Cough monitoring

We will install a microphone (RØDE NT-USB, Sydney, Australia) near the ceiling to continuously record the sounds in the waiting room (figure 1). CoughSense, a deep learning cough detection algorithm based on MXNet, an open-source deep-learning software framework, was developed to classify audio signals as coughing or other sounds.^24^ The algorithm uses spectrograms extracted from the raw audio for classification. The model was trained and tested using multiple audio recordings obtained through clinical and ambulatory deployments. We will identify audio records with cough sounds and calculate the cough frequency, intensity and duration. The cough data will be linked with the CO_2_ data and video sensor data by time and date. Finally, we will probabilistically link the video sensor data (ie, the moving dots) with the clinical data by the height of the patient, time and date of the visit.

#### Bio-aerosol sampling and molecular detection

We will collect Mtb particles from the air using mobile bio-aerosol sampling devices (Dry Filter Unit (DFU)1000, Lockheed Martin Integrated Systems, Gaithersburg, Maryland, USA). The DFU 1000 is a portable biological air sampler. Ambient air is drawn through 1 µm polyester-felt filters at a rate of ~1000 L/min via an electrical blower. The DFU is a useful collection system for low concentration aerosols, capturing particles of 1 µm or larger, and allowing easy access for the retrieval of filters. One DFU will be placed in the waiting room and the other in the TB treatment room (figure 1). Each DFU collects air for 7 hours (two periods of 3.5 hours) every day onto two filters. Due to logistical and human resource limitations, we will be able to change filters only two times per day. Therefore, we decided to run the mobile bio-aerosol sampling devices during the busiest time at the clinic, between 07:00 and 14:00. All other data will be collected from 07:00 to 16:00.

As previously described,^17^ duplicate filters from each sampling session will be transferred to 50 mL Falcon tubes and vortexed in sterile phosphate buffered saline (with 0.05% Tween 80). Following centrifugation at 3750 rpm for 15 min, filters will be removed and the pellet subjected to DNA extraction. DNA from Mtb cells will be extracted using an in-house lysis buffer with subsequent pelleting (centrifugation 13 000 rpm for 10 min) of DNA and resuspension in 50 µl of Tris-EDTA buffer (10 mM Trist, 1 mM EDTA, pH 8.0). Given that droplet digital PCR (ddPCR) is relatively robust against inhibitors, no further DNA purification will be required. The primer/probe combinations and reaction conditions for Mtb-specific ddPCR have been described.^16^ Samples with known amounts of purified Mtb DNA (0.01 ng and 0.001 ng) will be included to serve as positive and nuclease-free water as negative control. The data generated from the ddPCR reaction will be analysed via the Umbrella pipeline,^25^ using wells with a minimum of 10 000 droplets.

### Statistical analyses

We will describe the data and examine associations between sources of data and then use results to parameterise a mathematical model (table 1). The statistical analysis will quantify the joint association between the clinical and environmental variables and the number of Mtb particles measured by the mobile aerosol sampling. To this end, we will use Poisson regression, with the number of Mtb particles by the period of time as the dependent variable, considered as a proxy measure for the risk of TB transmission. As this variable is measured by periods of 3.5 hours, the other variables will be aggregated over the same periods. We will consider all combinations of independent variables, including second-order interactions, and compare the model using standard model selection methods. We will use variable selection methods in a Bayesian framework, including the deviance information criterion and the leave-one-out information criterion.^26^

**Table 1 T1:** Description of the measurements

Data source	Parameter	Description	Unit	Measurement taken by
CO_2_ monitor	CO_2_	Observed CO_2_ concentration in the indoor air per minute and a control in the outdoor air. Based on CO_2_ levels and people density, we will calculate rebreathed air volume, which is used as a proxy for airborne TB transmission.^16^	ppm	Minute and date
	Relative humidity	Data on the effects of relative humidity on the survival of airborne bacteria are inconsistent.^28 37^ However, a recent study found that relative humidity above 65% is associated with Mtb survival in the air.^14^	%	Minute and date
	Temperature	Temperatures above 24°C are required to reduce airborne bacteria survival.^28 37^	°C	Minute and date
Cough recording	Frequency	One of the typical symptoms of TB is coughing; coughing is also the main way of transmission.	n	Minute or day and date
	Duration	Duration of each cough is different from healthy and people with TB or other lung diseases^30^	s	Cough by minute and date
	Intensity	Intensity of each cough is different from healthy and people with TB or other lung diseases.^30^	dB	Cough by minute and date
Mobile aerosol sampling	Mtb DNA copies	Detection of Mtb particles in the air by filter or per day (07:00 to 14:00).^17^	Copies per microliters	Filter (ca.3.5 hours sampling) or per day
Video sensor	Number of people	From the raw data (x–y coordinates) we can calculate the number of people at a given location by 0.25 second and by minute.	n of people	0.25 s or min and by date
	Time spent at a given location	From the raw data (x–y coordinates) we can calculate for each person their time spent at different locations.	min	Minute and date
Patient charts	Number of registered patients	All patients who are visiting the clinic are registered.	n of registered patient	Minute and day
	Number of presumptive TB and of TB patients	From all registered patients we will know the number of presumptive TB cases and the number of patients with TB.	n of presumptive TB and TB patients	Minute and day

dB, decibel; Mtb, *Mycobacterium tuberculosis*; n, number; ppm, parts per million; s, second; TB, tuberculosis.

We will operationalise the variables as follows:

*Patient data*: Numbers and characteristics of patients consulting the clinic overall will be summarised using descriptive statistics.*Video sensor data:* Raw data about individuals’ movements will be transformed into waiting times until medical consultation, number of individuals in the different locations, highly frequented areas in the clinic and the average distance between patients (ie, clustering). We will link each tracked individual to the clinical data collected from the clinic’s database (ie, TB/HIV diagnosis), using the order of arrival and time of registration.*CO_2_ data*: Measurements of CO_2_ concentration at the different locations in the clinic (waiting room, registration desk, TB treatment room), together with estimates in outdoor air, will be used to estimate the proportion of air in the different locations that was expired by individuals, the rebreathed fraction.^12^ We will use a modified Wells-Riley model appropriate for non-steady states conditions of ventilation and number of individuals to describe and calculate the shared rebreathed air in the different locations in either litre/minute or litre/day and the air exchange (litre/hour per person). Table 2 describes the parameters to calculate the shared rebreathed air and the air exchange.^13 16 27 28^The proportion of rebreathed air (*f*) will be calculated from the excess CO_2_ measured indoors, divided by the exhaled CO_2_ (*Ca*):(1)$$f=\frac{\left(C-Co\right)}{Ca}$$(see table 2 for definitions of parameters in this and the following equations).Before we can calculate the rebreathed air volume (RAV) we will need the rebreathed proportion from other people (ƒo). Therefore, we need to know the number of people (*n*) present at each time point at the clinic:(2)$$fo=f\times \frac{\left(n-1\right)}{n}$$Finally, we can calculate the RAV for each minute by multiplying ƒo and the minute respiratory volume (8 L/min, *(p*)) as:(3)Rebreathedairvolume(RAV)=(pfo)In the next step, we aim to calculate the ventilation rate (air exchange). The indoor CO_2_ generated rate is the product of the average volume of gas exhaled per person (0.13 L/s per person, *(V*)) and the CO_2_ concentration of the exhaled air:(4)$$\begin{array}{c} IndoorCO_{2}generationrateinl/s\\ perperson\left(G\right)=VxCa \end{array}$$The ventilation rate is expressed as:(5)$$\begin{array}{c} Ventilationrateinl/sperperson\\ \left(Q\right)=\frac{G}{C-Co} \end{array}$$To calculate the air exchange per hour (Equation 6) we need to know the volume of air in a given location.*Relative humidity and temperature:* We will describe changes in relative humidity and temperature over the day.*Cough sounds*: Frequency, intensity, duration of recorded coughs per time period.^29 30^*Detection of Mtb in bio-aerosol sampling*: The number of Mtb genome copies present in each sample.

**Table 2 T2:** Description of the variables to calculate the shared rebreathed air volume and air exchange as well as the parameters to construct the mathematical transmission model

Parameter	Description	Value
C	Observed CO_2_ concentration in the indoor air per minute	Observed
Co	CO_2_ concentration in the outdoor air per minute	400–420 ppm^23^
Ca	CO_2_ concentration in the exhaled air	38 000–40 000 ppm^13 38^
f	Proportion of rebreathed air	Equation
n	Number of people recorded at the location	Observed
fo	Rebreathed proportion from other people	Equation
p	Minute respiratory volume	8 L/min^38^
RAV	Rebreathed air volume	Equation
V	Average volume of gas exhaled per person	0.13 L/s per person^16^
G	Indoor CO_2_ generation rate (L/s per person)	Equation
Q	Ventilation rate (L/s per person)	Equation
vol	Volume of the room	Calculated

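### DIC and leave-one-out act on the 3.5-hour period, so they do not suit the between-clinic comparison in hypothesis 3: without a clinic term they often select clinic-constant variables that have no effect

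*Protocol article*

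**What the plan says.** Hypothesis 3 in the Introduction is directional and compares clinics: "clinics with small and crowded waiting rooms, low ventilation and suboptimal patient separation have an increased risk of TB transmission". The number of clinics is open: "The study will take place at several antiretroviral therapy (ART) or primary care clinics" (Study setting and study population). The clinic-level data to be collected include "TB control measures (natural ventilation, use of masks, separation of patients with TB or coughers) and the floor plan of the clinics" (Patient and clinic data).

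Statistical analyses fixes the model ("we will use Poisson regression, with the number of Mtb particles by the period of time as the dependent variable"), the unit ("As this variable is measured by periods of 3.5 hours, the other variables will be aggregated over the same periods"), the search ("We will consider all combinations of independent variables, including second-order interactions, and compare the model using standard model selection methods") and the criteria ("We will use variable selection methods in a Bayesian framework, including the deviance information criterion and the leave-one-out information criterion"). It names no clinic term and no grouping for the leave-one-out step.

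Mathematical modelling refers to a 6-hour counting period, which does not match 3.5 hours. On either figure the observation is a period at a clinic, not a clinic.

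**The concern.** Leave-one-out (LOO) in its ordinary form removes one observation, here one filter period. The other periods from the same clinic stay in the fit, so the score measures how well a variable helps predict another period at a clinic already seen. Hypothesis 3 needs to know whether a feature distinguishes clinics, and there the effective sample size is the number of clinics.

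A feature that is constant within a clinic, such as room size or patient separation, partly labels the clinics. If clinics differ for any reason and the model has no clinic term, the label improves period-level prediction even when the feature has no effect. If clinic effects are in the model, each clinic's own level already predicts its omitted period, and the feature has almost nothing to add to the score even when it matters.

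At stake are conclusions about clinic layout and infection control. The Discussion says the wider study could inform guidelines and the planning of clinic infrastructure.

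**Working it through.** **Inputs from the article.** Two 3.5-hour periods a day per sampler (Bio-aerosol sampling). For the duration, Study design says "Data collection will take place for over 4 weeks"; I take about 20 workdays. Periods per clinic per sampler: 2 × 20 = 40. Omitting one leaves 39 from the same clinic.

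**Inputs assumed, because the article gives none.** Number of clinics K (3–10, mainly 4 and 8); mean count per period m (mainly 3–5); between-clinic SD of the log rate s (0–1.0); one covariate that is constant within each clinic. The plan has no figure of its own to reproduce.

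**Step 1: hand calculation, no clinic term, no true effect.** One extra parameter is preferred, approximately, when the likelihood-ratio statistic exceeds 2. If clinics do not differ, this has probability P(χ²₁ > 2) = 15.7%. If they differ, the variance of a clinic's log mean is 1/(nm) + s² while the model assumes 1/(nm). The statistic is then inflated by 1 + nm·s², and selection has probability P(|Z| > √(2/(1 + nm·s²))). With n = 40 and m = 3, nm = 120:
- s = 0.3: inflation 1 + 120 × 0.09 = 11.8; P(|Z| > 0.412) = 68%
- s = 0.5: inflation 31; P(|Z| > 0.254) = 80%
- s = 1.0: inflation 121; P(|Z| > 0.129) = 90%

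Half of each falls in the hypothesised direction: 34%, 40%, 45%. K does not enter the formula.

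**Step 2: simulation of the same case** (1,000 studies per cell, n = 40, m = 3, two-level clinic covariate, true rate ratio 1):

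| K | s | LOO selects | in hypothesised direction | DIC selects |
|---|---|---|---|---|
| 4 | 0 | 16% | 7% | 16% |
| 4 | 0.3 | 67% | 37% | 69% |
| 4 | 0.5 | 76% | 40% | 79% |
| 4 | 1.0 | 86% | 41% | 89% |
| 8 | 0 | 17% | 8% | 17% |
| 8 | 0.3 | 67% | 36% | 70% |
| 8 | 0.5 | 75% | 37% | 79% |
| 8 | 1.0 | 86% | 42% | 91% |

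DIC is approximated here by its AIC-type equivalent. Other implementations differ by a few points. Over means of 3–5 and 4–8 clinics, the ranges are about 67–92% (34–46% in the hypothesised direction), against 14–18% (7–9%) if clinics do not differ. The mean count matters: at K = 4 and s = 0.5 an exact calculation gives 55% for a mean of 0.5 copies and 85% for a mean of 20. Requiring a LOO gain above 2 standard errors at K = 4 still selects the null variable in about 18%, 37% and 56% at s = 0.3, 0.5 and 1.0.

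**Step 3: clinic random effects added, period-level LOO, s = 0.5.** Median gain in log predictive score for rate ratios 1, 2 and 3:
- K = 4: −0.01, −0.01, 0.00
- K = 8: −0.02, 0.00, +0.02

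The sign does shift (positive in 16% of studies at rate ratio 1 and 70% at rate ratio 3, K = 8). The size stays negligible: a gain above 2 standard errors occurs in 0–1% of studies in every setting.

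**Step 4: same model, posterior of the clinic-level coefficient.** A posterior probability above 0.975 for a harmful effect is reached in 0–2% of null studies. At s = 0.5 and K = 8 it is reached in 32% (rate ratio 2) and 62% (rate ratio 3); at K = 4, in 6% and 11%.

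**Step 5: leaving out a whole clinic.**
- Without a clinic effect in the model, the null covariate is still preferred in about 32–52% of studies.
- With the clinic effect integrated out, it is preferred in 29–41% at K = 4 and 18–22% at K = 8.
- With a true effect at s = 0.5, it is preferred in 62% and 79% (rate ratios 2 and 3) at K = 4, and 72% and 95% at K = 8.

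**Step 6: a null variable that varies between periods, clinic effects in the model.** Period-level LOO selects it in 14–18%, the usual rate.

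**The case against.** **The article never says that DIC or LOO decides hypothesis 3.** Table 1 lists only variables measured over time, and no section expressly enters room size or separation as a selection candidate. This stands as a limit on the claim. It does not dispose of it: the clinic features are collected, every combination of independent variables is to be compared, and no other tool for judging a variable is stated.

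**Clinic effects and grouped folds are ordinary SAP content, and this is a condensed article.** Agreed, so the unstated clinic term is not in itself the finding. But adding it removes only the false selection; Step 3 shows that the named LOO criterion then says almost nothing about clinic-constant variables.

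**Much of hypothesis 3 varies within clinics.** Crowding comes from the sensors and ventilation from minute-level CO₂. This stands: for those variables only the between-clinic part is affected.

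A reader might go further and infer three things that are not supported:
- *That hypothesis 3 will be confirmed when there is no effect.* The hypothesis is directional and the rate depends on a between-clinic variance that the article does not give.
- *That the hypothesis cannot be judged once clinic effects are included.* Only the LOO score loses its information; Step 4 shows the coefficient does not.
- *That the left-out unit is the whole fault.* Step 5 shows that changing it alone still prefers a null variable in about a third to a half of studies.

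**Conclusion.** The point holds in a limited form. The named criteria, applied to the stated unit, do not suit a between-clinic question. With the model as written, a clinic-constant variable with no effect is selected in about 67–92% of studies, roughly four to six times the rate when clinics do not differ (67/16 ≈ 4; 92/16 ≈ 6). In the hypothesised direction the rate is about 34–46%. These figures assume 4–8 clinics, 40 periods each, mean counts of 3–5 and a between-clinic log-SD of 0.3–1.0. Smaller SDs or very low counts reduce the excess, and it disappears if clinics do not differ.

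The Discussion also presents the results as generating hypotheses for later intervention studies, which tempers the consequence. The correction is still worth making before the multi-clinic data are analysed.

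**What to change.** In Statistical analyses:
- Include a clinic random effect in the Poisson model.
- Judge clinic-constant variables, and clinic means of crowding and ventilation, by the clinic-level coefficient with its interval. Support this with leave-one-clinic-out prediction: remove all filters of one clinic, predict them with the clinic effect integrated out, and report the score difference clinic by clinic.
- Keep DIC and period-level LOO only for variables that vary within a clinic, in a model with clinic effects.
- State the number of clinics, and call conclusions about clinic-constant features exploratory.

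The clinic effect and the change of left-out unit are both needed.

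Cost: a few sentences and one refit per clinic for each model compared, in Stan, which the article already plans to use; no new data. The price is precision. With few clinics the coefficient has little power, and leave-one-clinic-out still prefers a null variable in roughly 17–41% of studies, so fewer clinic features will be called drivers.
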